### Analyses

#### Baseline characteristics

The baseline characteristics of patients and operative details will be recorded.

#### Statistical analysis

Hazard of reherniation and of parenteral analgesia will be compared by treatment arms. Efficacy will be defined as 1 minus hazard ratio of active vs restricted arms. Efficacy less than absolute delta (see sample size) will be deemed equivalent. Change from baseline adjusted for baseline in functional scores will be compared across treatment arms. Magnitude difference will be compared using ranksum (Mann-Whitney-U) test.

Analysis will report both intention to treat and per protocol results. Per protocol adherence to treatment will compare time in movement by treatment arm using t-test allowing for differential variance**.** Time in movement should differ between arms. Two thresholds will be defined a priori – a sedentary level below which will be considered adherent to movement restriction, and an activity level above which non-restriction will be deemed to have occurred. These thresholds will be used to define adherence. In sensitivity analysis we will examine impact on trial outcomes of excluding those subjects allocated to restriction who moved above this threshold and those unrestricted who were sedentary. We will also conduct sensitivity analysis by cross allocating such subjects.

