### Hypothesis to be tested

That movement restriction following first episode lumbar microdiscectomy in adults results in improved outcomes in disc reherniation rates, pain and disability outcome measures.

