### Outcomes

#### Primary endpoints

While there is no widely used definition of clinical success following lumbar microdiscectomy it is generally accepted that such a definition should take account of outcome measures such as physical function, disability and pain [9–11]. Intervertebral disc reherniation and reoperation are important considerations as potential primary endpoints. In SPORT[12] 20% of patients who underwent surgery rated their progress as less than a major improvement at one year yet only 6% had undergone reoperation. Thus, reherniation and reoperation alone do not account for the majority of unsatisfactory patient outcomes following lumbar discectomy. The use of a composite endpoint allows for the capture of multiple outcomes that influence the overall success of a clinical intervention while also allowing for increased statistical efficiency and efficient resource utilisation [13, 14].

As such the primary endpoint to be assessed in this trial consists of a composite of the following widely accepted outcome measures:18 point reduction in VAS lower back25 point reduction in VAS legs15 point improvement in ODI scoreAbsence of disc reherniation (defined as repeat surgery at the same level)No other secondary intervention (epidural or nerve root injection, medial branch block)

Using the above definitions of treatment success we would anticipate treatment success rates of ~70–90% in keeping with those reported in the literature [8, 15]. This allows the ability to detect a clinically significant difference in outcomes between the two groups (i.e. rates of clinical success) with smaller groups than required for the detection of differences in recurrence rates (i.e. event rate of “clinical success” of approximately 70–90% as opposed to herniation event rate of 5–10%).

Utilisation of the personal wearable electronic device will enable accurate assessment of patient adherence to the allocated post-operative care group.

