#### Secondary endpoints

Secondary endpoints will consist of the following surgical and functional endpoints.

Surgical endpoints:Incidence to 12 months post-operatively of disc reherniation requiring repeat surgery at the same levelIncidence to 12 months post-operatively of other parenteral pain management intervention such as epidural or nerve root injection, medial branch block for the primary illness, but excluding enteral or dermal analgesia (fentanyl patches, TENS machine or acupuncture).

Functional endpoints:VAS lower back change scoreVAS legs change scoreODI change scoreDays to return to work (including days to return to modified duties and to normal duties.)

For functional endpoints, magnitude of change from baseline, adjusted for baseline score will be compared between treatment groups. Additionally, the proportion achieving predefined success thresholds (change scores of 18 for VAS back, 25 for VAS legs and 15 for ODI) will be compared.

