#### Sample size

As detailed earlier one randomised controlled trial investigating the role of post-operative activity restrictions in outcome following microdiscectomy has recently been reported [7]. The authors recruited 108 patients and noted disc reherniation rates of 11% in the 2-week restriction group and 9% in the 6-week restriction group. Previous studies have indicated a reherniation rate ranging from 2 to 18% [16]. Annual reported reherniation rates have been closer to 4–5% in large series [8, 17, 18]. The authors of the randomised controlled trial calculated it would be necessary to have 800 patients in each arm in order to detect a statistically significant difference in disc reherniation rate and that this may not be feasible. We are in agreement with this assessment.

Reported rates of clinical success for lumbar discectomy vary widely dependent on the criteria. Using the criteria detailed in our composite primary outcome we would anticipate a clinical success rate within the broad range reported in the literature of approximately 70–90%.

In determining the power of this study, we assume that approximately 80% of patients will meet the definition of treatment success. The calculation of sample size can be based upon a threshold of a 20% difference in treatment success as clinically significant (i.e. 80% success vs. 64% success). In order to have 80% power to detect a 20% difference in the binomial outcome of treatment success defined at *p* = 0.05 the sample size calculated would be 78 patients per group. If we allow for an approximately 30% drop-out rate, this will bring the calculated sample size to 105 patients per group for a total of 210 patients in the trial.

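### The Statistical analysis section never compares the composite primary endpoint and places its only decision rule, an equivalence verdict, on two secondary hazards

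*Protocol article*

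**What the plan says.** - **Primary endpoints:** "the primary endpoint to be assessed in this trial consists of a composite of the following widely accepted outcome measures". The components are thresholds on VAS back, VAS leg and ODI, no reherniation (repeat surgery at the same level) and no other secondary intervention.
- **Sample size:** the calculation uses the composite alone. It starts from "we assume that approximately 80% of patients will meet the definition of treatment success" and continues "In order to have 80% power to detect a 20% difference in the binomial outcome of treatment success", at p = 0.05. The result is 78 per group, raised to 105 per group (210 in total) for dropout. The same section endorses the view of an earlier randomised trial that about 800 patients per arm would be needed for reherniation and that this may not be feasible.
- **Secondary endpoints:** reherniation, parenteral pain intervention, the three change scores and return to work. The section adds: "Additionally, the proportion achieving predefined success thresholds (change scores of 18 for VAS back, 25 for VAS legs and 15 for ODI) will be compared".
- **Statistical analysis:** "Hazard of reherniation and of parenteral analgesia will be compared by treatment arms". Efficacy is then defined as one minus the hazard ratio, and a value below the delta of the sample size section is taken to show equivalence. Functional scores are also compared. Composite treatment success does not appear.
- **Hypothesis to be tested:** movement restriction "results in improved outcomes in disc reherniation rates, pain and disability outcome measures". The composite is not named.

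**The concern.** The endpoint that is primary and that fixes the sample size has no comparison in the section that says how the arms will be compared. The one sentence there that turns a result into a conclusion belongs to two outcomes the article calls secondary, and it takes its threshold from a calculation made for a different outcome. A trial team following the section literally would declare equivalence, or fail to, on reherniation and injection hazards. Primary endpoints explains that the composite was chosen so that groups could be smaller than differences in recurrence rates would require. The verdict would therefore come from an outcome the authors had already judged out of reach.

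**Working it through.** **1. Where delta comes from.** Inputs from Sample size: 80% versus 64% success, power 80%, p = 0.05 (taken as two-sided, since sidedness is not stated). The pooled formula, with mean proportion 0.72, is

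n = [1.96·√(2·0.72·0.28) + 0.842·√(0.80·0.20 + 0.64·0.36)]² / 0.16² ≈ 123 per group.

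The stated 78 is not reproduced. It is matched by 80% versus 60% without pooling: (0.16 + 0.24)·7.849 / 0.20² = 78.5. That mismatch is a separate matter. What counts here is that delta, whether 16 or 20 points, is a difference in the proportion with composite success. No reherniation or injection rate enters it.

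**2. The sections side by side.**

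| Outcome | Status | Trial sized on it | Compared in Statistical analysis | Decision rule there |
|---|---|---|---|---|
| Composite success | Primary | Yes | No | None |
| Reherniation | Secondary | No | Yes, hazard | Equivalence |
| Parenteral pain intervention | Secondary | No | Yes, hazard | Equivalence |
| VAS back, VAS leg, ODI change | Secondary | No | Yes | None |
| Threshold proportions | Secondary | No | No (stated under Secondary endpoints) | None |

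**3. What the reherniation hazard can show.** With 1:1 allocation, SE(log HR) ≈ 2/√d for d events, and the 95% interval is the estimate divided and multiplied by exp(1.96·SE).

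- Assumed rate 5% (the article cites 4–5% a year in large series): d = 210·0.05 = 10.5. SE = 2/√10.5 = 0.617 and the factor is exp(1.210) = 3.35. With d = 10 it is 3.45. Call it 3.4: an estimate of 1 has an interval of about 0.29 to 3.4.
- At 4%: d = 8.4, factor about 3.9. At 10% (the top of the range under Primary endpoints): d = 21, factor about 2.4.

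These figures assume full follow-up. Dropout widens them.

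**4. Could an interval ever support the rule?** Take delta as 0.20, so that the hazard ratio must exceed 0.80. With an estimate of 1, the lower 95% limit clears 0.80 only if 3.92/√d ≤ −ln 0.80 = 0.223, so d ≥ (3.92/0.223)² ≈ 309 events. With delta 0.16 (limit 0.84) it is (3.92/0.174)² ≈ 505 or so. Both exceed the 210 participants. This also covers the parenteral-intervention hazard, for which the article gives no event rate.

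**5. If only the point estimate is used.** With 10 events, SE = 0.632.

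- Rule read as |1 − HR| < 0.20. If the true HR is 1: Φ(0.288) − Φ(−0.353) = 0.613 − 0.362 = 25%. If the true HR is 2: Φ(−0.808) − Φ(−1.449) = 0.210 − 0.074 = 14%.
- Rule read without the absolute value (any estimate above 0.80). True HR 1: 1 − 0.362 = 64%. True HR 2: 1 − 0.074 = 93%.

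On the first reading the verdict hardly separates no effect from a doubled hazard. On the second it declares equivalence more often when the unrestricted arm does worse.

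**The case against.** Three points can be made for the article.

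First, it is a condensed account, and the test of the composite may stand in a full protocol or analysis plan that is not shown. That is fair for the missing test taken alone. But the section is not silent: it specifies a hazard-ratio measure, a rank-sum test, an unequal-variance t-test and cross-allocation sensitivity analyses, and it prints a verdict rule. An analysis plan that tested the composite would still contradict that rule, so the conflict is present in the text at hand.

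Second, the deciding comparison can be inferred. Primary endpoints speaks of detecting a difference in rates of clinical success, Sample size gives contrast, power and significance level, and Non-Adherence gives intention to treat. This stands. A reader might conclude that no comparison in the document decides the trial, and that would go too far. The defect is that the only explicit rule points elsewhere.

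Third, the hypothesis names reherniation, pain and disability, which are the main domains of the composite. This also stands. The hypothesis is loosely worded and should be aligned, but it does not by itself set up competing deciding endpoints.

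**Conclusion.** Wrong as written. The Statistical analysis section omits the comparison that Primary endpoints and Sample size make primary, and its sole decision rule gives an equivalence verdict to two secondary hazards using a delta from the composite. The planned 105 per arm compares with about 800 per arm that the article accepts for reherniation, and the hazard ratio would carry an uncertainty factor of about 3.4 each way (about 3.9 to 2.4 for rates of 4% to 10%). These figures rest on the assumed event rates, complete follow-up and the usual large-sample variance, which is rough at 10 events. The contradiction between sections needs none of these assumptions.

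Two stronger readings are not supported.

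- **An inflated false-positive rate.** Five tests, each at an assumed two-sided 0.05, would give 1 − 0.95⁵ = 22.6% if independent and about 13% at an assumed common correlation of 0.8, but only if any one result could decide the trial. The section states no significance level and no such rule, the outcomes are declared secondary, and the hazard rule concerns equivalence, not difference. So 13–23% is a conditional illustration and not this trial's error rate.
- **Frequent disagreement between the composite and reherniation tests.** A simulation of this would mainly show that reherniation is underpowered, which the article says openly, and it would replace the stated equivalence rule with a difference test.

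**What to change.** In Statistical analysis, state that the deciding analysis is the between-arm difference in the proportion with composite treatment success, by intention to treat, with its confidence interval, at the 0.05 level used in Sample size. Delete the equivalence verdict from the hazards of reherniation and parenteral pain intervention. Report those hazards, the three change scores and the three threshold proportions as supportive estimates with 95% confidence intervals and no verdict. Align the hypothesis so that it refers to composite treatment success.

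The cost is wording in two sections, with no extra data or patients. The small downside is that secondary results can no longer support stand-alone claims.

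### The equivalence rule bounds 1 − HR for two secondary events with a delta that belongs to the composite success proportion, and its sign is ambiguous

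*Protocol article*

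**What the plan says.** Three statements in the Statistical analysis section follow one another. The first names the outcomes: "Hazard of reherniation and of parenteral analgesia will be compared by treatment arms". The second sets the measure: "Efficacy will be defined as 1 minus hazard ratio of active vs restricted arms". The third sets the verdict: "Efficacy less than absolute delta (see sample size) will be deemed equivalent".

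The third sends the reader to the Sample size section for delta. The only candidate there is a "threshold of a 20% difference in treatment success as clinically significant (i.e. 80% success vs. 64% success", and the same paragraph calls the outcome binomial: "80% power to detect a 20% difference in the binomial outcome of treatment success". It belongs to the composite primary endpoint.

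The Secondary endpoints section lists reherniation needing repeat surgery and other parenteral pain intervention as secondary, both to 12 months. On reherniation, the Sample size section reports the view of an earlier randomised trial that it would be "necessary to have 800 patients in each arm in order to detect a statistically significant difference in disc reherniation rate", that this may not be feasible, and that the authors agree. The Question and Objectives sections ask whether the unrestricted arm is inferior.

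**The concern.** The rule takes a threshold set for one endpoint on one scale (a difference in success proportions) and applies it to two other endpoints on another scale (1 − HR for time to an event). A number such as 0.16 or 0.20 means something quite different in the two places.

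The direction is also open. The comparison is active against restricted, and the Investigational treatment section makes the unrestricted group the investigational arm. Excess reherniation without restrictions therefore gives HR > 1 and a negative efficacy, which lies below any positive delta. If the word absolute was meant to apply to efficacy, the rule is two-sided and behaves differently.

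At stake is an equivalence statement about reherniation, the harm that restrictions are meant to prevent. The Background says that a finding of no difference would let future patients resume normal activity quickly.

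**Working it through.** **1. Where delta comes from.** The Sample size section has 80% success ("we assume that approximately 80% of patients will meet the definition of treatment success"), 64% as the contrast, 80% power, and "0.05 the sample size calculated would be 78 patients per group".

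- As worded, detecting 80% against 64% at two-sided 0.05 needs n = (1.960 + 0.842)² × (0.80×0.20 + 0.64×0.36) / 0.16² ≈ 120 per group, not 78.
- Non-inferiority with 80% in both arms, a 16-point margin and one-sided 0.05 needs n = (1.645 + 0.842)² × (2×0.80×0.20) / 0.16² = 77.3, so 78. This matches exactly.
- Superiority of 80% over 60%, two-sided and unpooled, gives 78.5, so 79. This is close.

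The article does not say which was used. In every variant delta is a difference in composite success proportions and never a bound on 1 − HR.

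**2. Scale.** With risk p under restriction, the risk at hazard ratio HR is 1 − (1 − p)^HR. The HR that matches an absolute difference d is ln(1 − p − d) / ln(1 − p).

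| Risk p | HR 1.16 to 1.20 as a difference in points | 16 to 20 points as an HR |
|---|---|---|
| 5% | 0.8 to 1.0 | 4.6 to 5.6 |
| 10% | 1.5 to 1.9 | 2.9 to 3.4 |

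The 5% and 10% are the ends of the herniation event range in the Primary endpoints section.

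**3. What the rule accepts.**

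- Signed reading, 1 − HR < delta: met whenever HR > 0.84 (delta 0.16) or HR > 0.80 (delta 0.20), with no upper limit. HR 2 gives efficacy −1 and HR 3 gives −2, and both pass.
- Two-sided reading, |1 − HR| < delta: met for HR between 0.84 and 1.16, or between 0.80 and 1.20.

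**4. How often each reading is met.** Simulation with binomial events per arm and the estimated HR as the ratio of cumulative hazards. Assumptions: 105 per arm with no losses, and true HRs chosen for illustration. Ranges cover delta 0.16 to 0.20.

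| Risk under restriction | True HR | Signed | Two-sided |
|---|---|---|---|
| 5% | 1 | 59–62% | 17–22% |
| 5% | 2 | about 95% | 10–12% |
| 5% | 3 | about 99% | about 2% |
| 10% | 1 | 65–69% | 28–35% |
| 10% | 2 | about 99% | 6–8% |

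**5. Information available.** At HR 1, reherniations expected in total are 2 × 105 × 0.05 = 10.5, up to 2 × 105 × 0.10 = 21. With 10.5 events the 95% CI factor for the HR is exp(1.96 × √(4/10.5)) = 3.35, so the interval runs from about 0.30 to 3.35. With 21 events the factor is 2.35.

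**6. Power of a rule on the composite.** With 80% success in both arms and a 16-point margin, SE = √(0.32/n) and power = Φ(0.16/SE − z).

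- n = 78: SE = 0.0641. Power is 80% for a one-sided 0.05 bound (90% CI) and 70% for a two-sided 95% CI.
- n = 73 (105 less 30%): SE = 0.0662. Power with the 95% CI is 68%.
- For 80% power with the 95% CI: n = (1.960 + 0.842)² × 0.32 / 0.16² = 98.1, so 99 per group.

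**The case against.** **The signed reading may not be meant.** Equivalence is normally two-sided, and in condensed prose the word absolute may have been intended for efficacy. On that reading a true HR of 2 or 3 usually fails. A reader might infer that the plan simply declares equivalence when reherniation doubles or triples. The text does not settle this, so the sign is an ambiguity to be resolved. Nor is the two-sided rule a coin toss: at a 10% rate it is met about four to five times as often at HR 1 as at HR 2. It is weak, but it does fall with harm.

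**The rule concerns secondary endpoints.** A reader might infer that it delivers the trial's overall verdict. The article does not say so. The primary endpoint is the composite, and an analysis of it may stand in a statistical analysis plan that is not shown.

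**The missing confidence interval may be left to that plan.** This stands, and it is not counted as a separate defect. An interval added later would still be compared with a delta from the wrong scale and endpoint.

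**The 20% is at least a ratio-type figure,** since 64/80 = 0.80. But it is a ratio of success proportions, not of event hazards.

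**Only reherniation can be sized.** The documents give no rate for injections, so nothing is computed for them.

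The mismatch of scale and endpoint survives all of these, under either reading.

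**Conclusion.** The concern holds as a mismatch of scale and endpoint in a rule that the protocol itself fixes, with an ambiguous sign on top. The mismatch follows from the text and needs no assumption. Its size at 5% reherniation is roughly a 0.8 to 1.0 point difference on the hazard reading, against an HR of 4.6 to 5.6 if the 16 to 20 points were meant literally.

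Neither reading of the sign gives a usable rule. One is met more often as harm grows. The other misses true equality in about two thirds or more of trials, yet still passes a doubled hazard in 6–12%. These frequencies rest on 105 per arm without losses, reherniation of 5–10% and illustrative hazard ratios. Either way an equivalence verdict would rest on about 10 to 21 reherniations, for an outcome on which the protocol agrees that about 800 per arm would be needed. This should be corrected before analysis.

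**What to change.** 1. Delete the equivalence rule for the hazard ratios. Report the reherniation and parenteral-intervention hazard ratios with 95% CIs as secondary results, without an equivalence claim.
2. Put the decision on the composite primary endpoint: the difference in success proportions, unrestricted minus restricted, judged by a confidence bound against a margin stated in percentage points. State the confidence level.
3. Justify the margin. The present threshold is framed as a difference to detect, and it is given both as 20% and as 80% against 64%. Neither becomes a non-inferiority margin without an argument.

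The change is to wording and needs no new data, but it has a cost in power that should be disclosed. With a 16-point margin and 80% success in both arms, a one-sided 0.05 bound keeps the stated 80% power at 78 per group. A two-sided 95% CI gives about 70% at 78 and 68% at 73. If the 95% CI is chosen, the power must be restated, or the size raised to 99 evaluable per group (99/0.70 ≈ 142 with 30% drop-out).

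### Change in VAS back, VAS leg and ODI is to be compared adjusted for baseline, but the only test named for that comparison is a plain rank-sum test with no baseline term

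*Protocol article*

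**What the plan says.** Under Secondary endpoints, the protocol article lists change in VAS lower back, VAS legs and ODI as functional endpoints and states: "For functional endpoints, magnitude of change from baseline, adjusted for baseline score will be compared between treatment groups".

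Under Statistical analysis it repeats the intention: "Change from baseline adjusted for baseline in functional scores will be compared across treatment arms". The next sentence gives the method: "Magnitude difference will be compared using ranksum (Mann-Whitney-U) test".

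No other method is named for the size of change in these scores. Analysis of covariance, regression, a stratified rank test, rank analysis of covariance and a rank test on residuals are all absent. According to Follow up schedule, the questionnaires are completed before surgery, so the baseline values will exist.

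**The concern.** The stated comparison and the stated test do not fit together. Secondary endpoints uses the word *magnitude* for the baseline-adjusted change, and Statistical analysis uses the same word for what the rank-sum test compares. The natural reading is that the rank-sum test is meant to carry out the adjusted comparison, and in its ordinary two-sample form it cannot.

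Two things are at stake. The first is precision: an unadjusted comparison of change generally wastes information in the baseline score, although how much is uncertain here. The second is pre-specification: if the adjusted analysis is intended but undefined, the analyst must choose between an unadjusted rank test and some adjusted model, possibly after seeing the data. Bias is not the issue, because randomisation protects the unadjusted comparison on average.

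**Working it through.** **Side by side.** Two sentences, in two sections, promise adjustment for baseline. One sentence names a test, and that test takes two groups of values and no covariate. Either the rank-sum test is the analysis, and the adjustment is missing, or it is a separate unadjusted analysis, and the adjusted one has no method. The text needs correcting on both readings.

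**Plan's own figure.** The article gives no sample size, SD or correlation for the functional scores, so there is no figure to reproduce on this point. Its only sample-size figure, 78 per group, belongs to the composite primary endpoint and is used below only as a convenient group size. (It has a difficulty of its own: with 80% and 64%, two-sided 0.05 and 80% power, the unpooled formula gives 7.849 × (0.16 + 0.2304) / 0.16² = 119.7 per group. That is a separate matter.)

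**Inputs, all assumed.** r is the correlation between baseline and follow-up score; k is baseline SD divided by follow-up SD. Set the follow-up SD to 1, so the baseline SD is k.

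**Formulae, per patient.**
- Unadjusted change: variance = 1 + k² − 2rk.
- Analysis of covariance: residual variance = 1 − r².
- Ratio = (1 − r²) / (1 + k² − 2rk).

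| k | r = 0.3 | r = 0.5 |
|---|---|---|
| 0.6 | 0.91 / 1.00 = 0.91 | 0.75 / 0.76 = 0.99 |
| 1.0 | 0.91 / 1.40 = 0.65 | 0.75 / 1.00 = 0.75 |
| 1.5 | 0.91 / 2.35 = 0.39 | 0.75 / 1.75 = 0.43 |

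The extra patients that an unadjusted mean-change comparison needs for equal precision are 1/ratio − 1. That is about 54% and 33% at k = 1, and about 10% and 1% at k = 0.6.

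**Why the ratio never exceeds 1.** The denominator minus the numerator is (1 + k² − 2rk) − (1 − r²) = (k − r)², which is never negative. The two are equal only when k = r, that is, when the slope of follow-up on baseline, r/k, is 1.

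**The rank-sum test itself.** The ratio above is against a mean-change comparison, not against the test the article names. With normal scores and k = 1, the efficiency of the rank-sum test on change relative to analysis of covariance is (1 + r)/2 × 3/π. At r = 0.5 this is 0.75 × 0.955 = 0.72. A simulation (78 per arm, bivariate normal, k = 1, 4,000 runs per value of r, effect set for 80% power under analysis of covariance) gave these powers:

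| r | Analysis of covariance | t-test on change | Rank-sum on change |
|---|---|---|---|
| 0.3 | 79% | 61% | 59% |
| 0.5 | 80% | 68% | 65% |
| 0.8 | 79% | 74% | 72% |

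Under these assumptions most of the loss comes from not adjusting. The rank step adds two to three percentage points.

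**The case against.** The best defence is that the two sentences in Statistical analysis describe two analyses: an adjusted comparison whose model is left to a fuller document, and a rank test beside it. A rank-sum test on baseline-adjusted residuals would also satisfy both sentences. This stands to the extent that a reader might infer that no adjustment will take place, and the article does not establish that. It does not remove the point, because the one method the article fixes has no baseline term and nothing says which analysis is the main one.

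Other stronger readings are tempting and are not supported:

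- *The test yields no estimate in points.* Inverting the rank-sum test gives a Hodges-Lehmann shift with a confidence interval in VAS or ODI points. It would be unadjusted, but it exists.
- *Inferiority on pain and disability therefore cannot be judged.* The article states no margin in points for VAS or ODI, and its only equivalence rule is written for a hazard ratio. Changing the test would not supply a margin. The proportions reaching the success thresholds are also to be compared.
- *A fixed saving of 33% to 54%.* Those figures require equal SDs at baseline and follow-up and are set against a mean-change comparison. At k = 0.6 the saving falls to about 1% to 10%; at k = 1.5 it is larger.
- *Return to work is caught by the same fault.* It sits in the functional list and has no baseline score, so the sentence under Secondary endpoints is loosely worded. Statistical analysis, however, speaks of functional scores, and the handling of patients who do not return is commonly left to the analysis plan.

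It is also fair that with heavily skewed scores the rank step may cost nothing.

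**Conclusion.** The point holds as an inconsistency in a method the article has fixed, not as an omission. For VAS back, VAS leg and ODI, the article promises adjustment for baseline and names a test without it. The effect is limited to secondary endpoints; the composite primary endpoint and its sample size do not use this test.

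The size cannot be settled from the document. Against an unadjusted mean-change comparison, the gain from adjustment runs from almost nothing (ratio 0.99 at k = 0.6, r = 0.5) to more than halving the variance (0.39 at k = 1.5, r = 0.3), with r and k both assumed. The power figures for the rank-sum test also assume normal scores and equal SDs. What holds for any r and k is that, in large samples, analysis of covariance is never less efficient than the unadjusted mean-change comparison. That guarantee does not extend to a rank test on skewed data.

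**What to change.** In Statistical analysis, replace the rank-sum sentence by naming analysis of covariance as the analysis of each of the three functional scores, with arm and baseline score as terms. The outcome may be the follow-up score or the change score: with baseline in the model, both give the same arm effect. Report the adjusted difference in points with a 95% confidence interval. Keep the rank-sum test on change as a sensitivity analysis, labelled unadjusted. Use the same description under Secondary endpoints, so that the two sections agree.

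Naming one adjusted method is enough to resolve the conflict; a model across all visits would be a preference, not a requirement. The cost is wording only, since the scores are already collected before surgery. The change should be made before outcome data are examined by arm.
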